### Sample size

The sample size is driven by the VIBRA trial [22]. We assume that to achieve the VIBRA trial [22] sample size (minimum 262 HIV-positive individuals not on ART) by testing about 10,000 individuals in 100 villages, based on a previous trial [32]. According to a previous home-based HIV-testing campaign [33], we estimate an HIV-testing coverage rate of individuals aged 12 years or older in rural villages of 63%. We consider a 15% increase in coverage as relevant from a policy perspective. Using an intra-cluster correlation (ICC) of 0.028, with a sample of 100 clusters, we will require a sample size of 450 in order to have > 90% power to detect an increase in coverage rates to 78% or higher. This corresponds to an increase of 1.17 (variance inflation factor (VIF)) from the 386 individuals required in the absence of clustering. If we vary the ICC for villages and include an additional ICC for clustering at the household level [34], the maximum VIF would be 8.3 corresponding to a maximum sample size of 3204 needed to ensure 90% power to detect a 15% difference, well below the expected 10,000 individuals to be included. Table 3 displays the sample size calculations considering all relevant factors under different scenarios.

**Table 3 Tab3:** Sample size estimations for the HOme-based SElftestiNG (HOSENG) trial

Average village size	Average household size	ICC (village)	ICC (household)	VIF	Total number of clusters	Total sample size
30	2	0.028	0.05	1.04	100	402
30	2	0.028	0.1	1.07	100	413
30	2	0.05	0.05	1.20	100	462
30	2	0.05	0.1	1.34	100	518
30	2	0.1	0.05	2.95	100	1139
30	2	0.1	0.1	4.4	100	1699
30	4	0.028	0.01	1.06	100	410
30	4	0.028	0.05	1.31	100	507
30	4	0.028	0.1	1.62	100	628
30	4	0.028	0.5	4.12	100	1592
30	4	0.05	0.01	1.09	100	420
30	4	0.05	0.05	1.44	100	556
30	4	0.05	0.1	1.88	100	726
30	4	0.05	0.5	5.4	100	2085
30	4	0.1	0.01	1.15	100	442
30	4	0.1	0.05	1.73	100	668
30	4	0.1	0.1	2.46	100	950
30	4	0.1	0.5	8.3	100	3204

*ICC* intracluster correlation coefficient, *VIF* variance inflation factor

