### Analyses

Analyses will be reported following Consolidated Standards of Reporting Trials (CONSORT) guidelines for cluster-randomized trials [35]. Clusters will be set as the unit of randomization (stratified by district, size of village, and village access to the nearest health facility), whereas individuals are set as the unit of analysis. An intention-to-treat set will be used, i.e., all study participants will be evaluated according to arm assignment at randomization. The primary analysis will use multi-level logistic regression models including village and household as random effects to assess the difference between HIV-testing coverage in the intervention versus the control arm. These models will be adjusted for the pre-specified randomization stratification factors and relevant baseline factors (age groups, gender, education status, employment status, HIV-testing history) that may be randomly unbalanced between intervention and control clusters [36, 37].

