Baseline characteristics will be presented according to randomized groups; no formal testing will be performed. Categorical variables will be described with absolute and relative frequencies and continuous variables with medians and interquartile ranges. As with the primary analysis, secondary endpoints will be analyzed with multi-level logistic regression models including village and household as random effects. All results will be presented as odds ratios and 95% confidence intervals. The potential effect modification of sociodemographic determinants (age groups, gender, education status, employment status, HIV-testing history) on all endpoints will be assessed by including interaction terms in the models. If the Wald test results for the interaction terms are significant, intervention effects will be presented separately by the levels of these factors. Sensitivity analyses will be conducted in order to provide evidence that the result seen from the primary analysis are robust. In order to assess the reliability of the model fit, we will perform a quadrature check. In case of unreliable model fit, we will use generalized estimating equations to fit our model which will provide population-averaged odds ratios and 95% confidence intervals. However, this model would not allow inclusion of more than one random effect although including the highest level of clustering is suggested to be sufficient [38]. All analyses will be done using Stata (version 14, Stata Corporation, Austin, TX, USA). For all tests, we will use two-sided *p* values with an alpha = 0.05 level of significance.

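### The interaction Wald tests assume that, within each arm, a person-level factor has the same effect in every village; if it does not, they reject too often, by an amount the protocol gives no basis to fix

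*Protocol article*

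**What the plan says.** In the Analyses section of the protocol article, the primary comparison uses "multi-level logistic regression models including village and household as random effects to assess the difference between HIV-testing coverage" between arms. The same structure is carried over to the other outcomes: "secondary endpoints will be analyzed with multi-level logistic regression models including village and household as random effects".

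Effect modification is then examined for "sociodemographic determinants (age groups, gender, education status, employment status, HIV-testing history"), and it "on all endpoints will be assessed by including interaction terms in the models". The decision rule is explicit: "If the Wald test results for the interaction terms are significant, intervention effects will be presented separately by the levels of these factors". The level is general: "we will use two-sided *p* values with an alpha = 0.05 level of significance".

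No random slope, robust variance or village-level check is named for these tests. Generalized estimating equations replace the multilevel model only if a quadrature check shows an unreliable fit. The section adds that this fallback could not hold more than one random effect. That remark counts village and household as the random effects, which supports reading them as two random intercepts, although the word intercept does not appear.

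**The concern.** Villages are randomized, while gender, age group and the other factors vary between people inside a village. An arm-by-gender interaction therefore compares the men-women gap in about 50 villages with the gap in about 50 others, and its precision depends partly on how much that gap differs from village to village.

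A village intercept raises or lowers men and women together, so it cannot represent a village where the gap is unusually wide. The interaction term lets the gap differ between arms. Within an arm, the model holds it constant on the log-odds scale. If the gap does vary, the Wald standard error treats that variation as individual-level noise spread over about 10,000 people and comes out too small. The test can then reject when the intervention effect is the same in men and women.

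A significant result decides whether effects are shown by level, so spurious subgroup differences could be reported too often.

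**Working it through.** **The plan's own figure.** For 63% versus 78%, two-sided alpha 0.05 and 90% power, the mean proportion is 0.705 and n per arm = [1.96·√(2·0.705·0.295) + 1.2816·√(0.63·0.37 + 0.78·0.22)]² / 0.15² = 192.2, rounded up to 193. Two arms give 386, as stated in the Sample size section. Then 386 × 1.17 = 451.6, against the stated 450. The inputs are being read correctly.

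**Inputs from the document.** The Sample size section plans on "by testing about 10,000 individuals in 100 villages", so m = 10,000/100 = 100 people per village, with 50 villages per arm. Coverage is p = 0.705, midway between 63% and 78%. The design village ICC is 0.028.

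**Assumptions not in the document.** These are q, the share of people with the factor (0.5 unless stated), and tau, the between-village SD of the factor's log odds ratio.

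**Analytic check.** Within one village the factor's log odds ratio has sampling variance of about 1/[m·q(1−q)·p(1−p)]. Slope variation adds tau². So

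true variance / model variance = 1 + tau²·m·q(1−q)·p(1−p) = 1 + tau² × 100 × 0.25 × 0.208 = 1 + 5.2·tau²

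rejection = 2·[1 − Φ(1.96/√ratio)]

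At tau = 0.3 the ratio is 1.468, 1.96/1.212 = 1.618, and rejection is 10.6%.

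**Simulation check.** There were 1,500 trials per setting, with households of 4 (2 men, 2 women), no true interaction, and a logistic model with village and household random intercepts. The comparator is a t-test on village-specific log odds ratios, which allows the gap to vary. The Monte Carlo standard error at 5% is √(0.05·0.95/1500) = 0.6 percentage points.

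| tau | Analytic, m = 100 | Planned Wald, m = 100, ICC village 0.028, household 0.1 | Planned Wald, m = 100, ICC village 0.05, household 0.5 | Planned Wald, m = 32, ICC village 0.028, household 0.1 |
|---|---|---|---|---|
| 0 | 5.0% | 4.7% | 5.2% | 5.5% |
| 0.2 | 7.5% | 7.3% | 7.0% | 6.3% |
| 0.3 | 10.6% | 10.3% | 9.3% | 7.0% |
| 0.5 | 19.6% | 18.7% | 16.7% | 9.5% |

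The village-level comparator stayed between 4.3% and 5.7% in all of these settings.

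**Linking tau to the design ICC.** The village variance is 0.028/0.972 × π²/3 = 0.0948 (SD 0.31). If male and female village effects each have this variance and correlation rho, then tau² = 2 × 0.0948 × (1 − rho).

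| rho | tau | Variance ratio | Rejection |
|---|---|---|---|
| 1 | 0 | 1 | 5.0% |
| 0.9 | 0.138 | 1.10 | 6.1% |
| 0.8 | 0.195 | 1.20 | 7.3% |
| 0.5 | 0.308 | 1.49 | 10.9% |

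With q = 0.2 instead of 0.5, q(1−q) falls from 0.25 to 0.16, and the last row becomes 8.7%.

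**Does the remedy hold its level?** A separate simulation without the household level (1,500 trials per setting) fitted a village random-intercept model and tested the same fits both ways. At ICC 0.028 and rho 0.5 the model-based test rejected 9.7% and the village-clustered sandwich test 5.1%. At ICC 0.05 and rho 1, where nothing needs correcting, the figures were 4.9% and 5.3%. Over all settings run, the sandwich test stayed between 5.1% and 5.7%.

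**The case against.** The strongest reply is that a condensed protocol need not name a variance estimator or random slopes for supportive interaction tests, and that clustered standard errors are compatible with every word of the section. Part of this stands: intercepts are the natural reading, not the literal one. But the section does fix the model, the test and the level, and read as written it gives the model-based Wald test. Its safeguards do not help. A quadrature check concerns numerical integration and would not reveal a missing slope, and the fallback model is used only if that check fails.

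The second reply is that the size depends on an SD that appears nowhere in the document, and that with a constant factor effect there is no defect. This stands in full.

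A reader might infer that these tests reject two to four times too often. The document does not support that as a headline. It requires an SD of about 0.3 to 0.5 at 100 people per village. Reaching 22.7% in the simulation without households took a village ICC of 0.1, the top of the range in Table 3, together with rho 0.5. A 50/50 split is also the worst case for a binary factor, and age group, education, employment and testing history were not simulated.

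A reader might also infer that the level-specific intervals are shown to be too narrow. No coverage was computed for them, so that is not established here.

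**Conclusion.** The point holds in conditional form. As written, the effect-modification tests assume a common factor effect across villages within each arm, and their type I error exceeds 5% to the extent that this fails. With 100 villages of about 100 people and a 50/50 factor, the error is nominal at SD 0, about 7% at SD 0.2, about 10% at SD 0.3 and about 19% at SD 0.5. At the design ICC of 0.028 the range is about 5% to 11% for rho from 1 to 0.5. At 32 people per village it is about 6% to 10% for SD 0.2 to 0.5. These figures rest on an assumed SD, on random intercepts as the reading of the model, and on gender as the worked example.

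The primary comparison of arms is not affected, because there the village intercept carries the between-village variation. This is a cheap improvement to a supportive analysis and does not threaten the trial's main conclusion.

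**What to change.** Add one sentence to the Analyses section: the interaction Wald tests, and the level-specific odds ratios they trigger, use village-clustered robust standard errors from the same multilevel model. A village-level random slope for the factor being tested is an acceptable alternative. The models otherwise stay as they are.

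The cost is one option in the model call and no new data. Intervals for the interactions will be somewhat wider when factor effects do vary by village, and the random-slope version may need some convergence work.

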### Monitoring, auditing, and data safety and monitoring board

At least one external monitoring visit will assess adherence to the approved trial protocol, accuracy of completed study forms, and the electronic dataset. The principal investigator agrees to allow inspectors from regulatory agencies to review records and will assist the inspectors in their duties, if requested.

The HOSENG trial represents implementation research and the oral HIVST is a well-established diagnostic tool. Thus, we do not expect serious adverse effects (SAE) on patients’ health from this intervention. However, for the purpose of this trial, we will try to capture the following SAEs: (1) Death due to any reason (especially within 30 days of a positive HIVST results), (2) Hospitalisation due to self-inflicted injuries within 30 days of a positive HIVST results, and (3) Hospitalisation resulting from violent assault by others (intimate partner violence, assault by family or community members) within 30 days of a positive HIVST result. The campaign team members all have several years of experience in HTC and received an additional study-specific, 1-week training in order to handle adverse events related to testing stigma. A separate, detailed safety monitoring plan will be developed to handle these SAEs in line with Swiss and Basotho ethics regulations. It is not planned to establish a data safety and monitoring board.

## Discussion

HIV-testing constitutes the “front door” to reach the UNAIDS 90-90-90 targets [39]. Currently, UNITAID invests US$23 million into a 4-year research initiative, called STAR, to gather evidence and catalyze the market for HIVST, and eventually improve testing coverage through HIVST in three African countries (Malawi, Zambia, and Zimbabwe) [40]. Whereas the STAR trials assess HIVST on a large scale, the HOSENG trial will focus on the use of oral HIVST during home-based HIV-testing campaigns. As such, its result will be complementary to the findings of the STAR project.

Home-based HIV-testing campaigns have been shown to be very effective in achieving high testing uptake, especially in resource-limited countries [7]. However, one major question is still unanswered: How to reach the absent people during these campaigns in a cost-effective way? The HOSENG trial tests whether oral HIVST may be an effective add-on during door-to-door testing campaigns towards achieving optimal testing coverage. Linkage to further testing and care after usage of oral HIVST will be provided by the VHWs, a trusted and long-standing public-sector cadre. VHW programs exist in all countries of Southern Africa and are being expanded [41]. If cost-effective, the HOSENG approach could easily be scaled up in the region, as the provision of oral self-test kits, followed up by VHWs, requires little additional human resources, finances, and logistics. The HOSENG trial will inform home-based HTC policies not only in Lesotho, but in similar nations in sub-Saharan Africa. However, we will have to closely monitor the linkage after testing and the additional burden of work for the VHWs.

## Trial status and recruitment

The trial has been launched on 26 July 2018 in both study districts. The recruitment time is driven by the VIBRA trial [22], as the HOSENG trial is the main recruitment platform for the VIBRA trial [22]. We assume a recruitment period of 6–8 months.

## Data Availability

The datasets used and/or analyzed during the study will be available from the corresponding author on reasonable request. The filled-in SPIRIT checklist was uploaded as Additional file 1.

## Abbreviations

ADORE: ADolescent ORal sElf-testing
ART: Antiretroviral therapy
GET ON: GETting tOwards Ninety
HIV: Human immune deficiency virus
HIVST: HIV self-test/ing
HOSENG: HOme-based SElftestiNG
HTC: HIV-testing and counseling
ICMJE: International Committee of Medical Journal Editors
SAE: Serious adverse events
Swiss TPH: Swiss Tropical and Public Health Institute
TB: Tuberculosis
UNAIDS: United Nations Programme on HIV/AIDS
VHW: Village health worker
VIBRA: Village-Based Refill of ART
VIF: Variance inflation factor
VMMC: Voluntary medical male circumcision
WHO: World Health Organization
